# Piloting Digital Navigators to Promote Acceptance and Engagement With Digital Mental Health Apps in German Outpatient Care: Protocol for a Multicenter, Single-Group, Observational, Mixed Methods Interventional Study (DigiNavi)

**DOI:** 10.2196/67655

**Published:** 2025-09-25

**Keywords:** digital therapeutics, digital health, digital health applications, digital health app, digital health apps, digital navigator, digital navigators, digital intervention, digital interventions, eHealth, mHealth, mobile health, digital health literacy, mental health, psychiatric care

## Abstract

**Background:**

In Germany, patients often have to wait several months for psychotherapeutic treatment. Digital therapeutics (DTx) offer a promising approach for timely mental health support, but their use remains limited. Digital navigators (DNs) are specially trained medical assistants who support other health care professionals (HCPs) in selecting and using DTx. This can improve digital health literacy, increase engagement, and reduce the burden on HCPs.

**Objective:**

The DigiNavi study is the first pilot study that aims to test the feasibility of implementing DNs in general practice and outpatient psychiatric care in Germany.

**Methods:**

This mixed methods study took place at six study sites (three psychiatric outpatient clinics, three general practices) in Germany. In the prestudy, patients and HCPs participated in semistructured interviews and focus groups concerning their acceptance and expectations of DNs (phase I). The Harvard Digital Navigator Training (HDNT) was adapted, and medical assistants were trained as DNs (phase II). During the intervention, 8 patients per site (N=48) diagnosed with a mental disorder were recruited via convenience sampling and supported by DNs in using DTx for mental health for 12 weeks (phase III). Patients’ (N=48) and HCPs’ (N=18) digital health literacy, digital and technical literacy, readiness and ability to change, and clinical symptom severity were assessed before and after 12 weeks of DTx prescription and support by DNs. Patient engagement with the DiGAs (usage duration and intensity) was measured after the intervention. Quantitative data were analyzed using a pre-post design. Finally, qualitative interviews were conducted with HCPs, patients, and DNs to explore their experiences with DNs, including perceived implementation barriers.

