**Results:**

The study received funding in July 2024. The prestudy including 35 participants was conducted from August to October 2024. HDNT adaptation and DN training were conducted from October to December 2024. Recruitment and quantitative baseline data collection started in December 2024, and 48 participants were enrolled by the end of March 2025. The intervention study ended in June 2025. Result dissemination and the development of strategies for the long-term implementation of DNs into the German health care system are planned until September 2025. We hypothesize that the provision of support by DNs will enhance patients’ and HCP’ digital and technical literacy, patient engagement with DiGAs, and readiness and ability to change. In addition, patients’ mental health is expected to improve after the end of the intervention.

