### Data Collection and Analysis

The following sections provide a concise overview of the data collection procedures (primary and secondary measures). All primary and secondary outcomes will be assessed before and after the 12-week intervention (pre- and postassessment). For an overview of enrollments, interventions, and assessments, see Multimedia Appendix 3. The subsequent sections offer a comprehensive description of the specific data collection procedures that were implemented in each phase of the study.

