#### Primary Outcome Measures

One primary outcome measure will be the impact of DNs on patients’ and HCPs’ digital health literacy. Digital health literacy will be assessed with two validated instruments, the Revised German eHealth Literacy Scale (GR-eHEALS) [49,50] and the Digital Health Literacy Index (DHLI) [51], which can already detect changes in smaller samples [52], before and after the 12-week intervention. The eHealth Literacy Scale (eHEALS) is the most widely used international questionnaire for the assessment of digital health literacy. It is a self-assessment tool that focuses on digital information–seeking skills [50]. We used the GR-eHEALS instead of the original eHEALS to ensure linguistic and cultural appropriateness for our German-speaking target group, since it is an adapted and validated version that considers language nuances and health care system specifics relevant to Germany [49]. The DHLI complements the GR-eHEALS in assessing interactive skills, such as the use of (web-based) health apps [51]. Further important primary outcome measures were the digital and technical literacy of patients and HCPs, their readiness and ability to change, as well as patients’ engagement with DiGAs. The following self-assessment instruments were used for this purpose: the information and communication technology (ICT) Self-Concept Scale [53], the Brief Scale of Technological Readiness [54], and the Digital Use survey from Harvard University and the Readiness for Change survey [55]. Engagement with DiGAs was assessed via structured interviews conducted by the study team.

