#### Secondary Outcome Measures

As a secondary outcome measure, the severity of the patient’s disease was assessed and compared before and after the intervention using validated scales. This measure allowed for a comprehensive evaluation of the symptom burden, functional status, and overall clinical improvement.

The Global Assessment of Functioning (GAF) [56] and the Clinical Global Impression (CGI) [57] scales are brief clinician-rated tools that capture the clinician’s view of the patient’s overall functioning and treatment response and are widely used to evaluate symptom severity and improvement. To assess specific symptom domains, the following instruments were used: the Hamilton Anxiety Rating Scale (HAM-A) [58], which is an instrument that measures the severity of anxiety symptoms, and the Hamilton Depression Rating Scale (HDRS) [59], which evaluates depressive symptomatology across multiple dimensions, including mood, sleep, and somatic complaints. These clinician ratings were complemented by the Beck Depression Inventory-II (BDI-II) [60], a widely used self-report questionnaire that captures the patient’s subjective experience of depressive symptoms. Additionally, sleep quality was assessed using the Insomnia Severity Index (ISI) [61], a brief self-report measure that evaluates the nature, severity, and impact of insomnia, which often co-occurs with mental health conditions and may influence treatment outcomes.

Table 1 provides an overview of the instruments used for data collection and analysis. The specific methodological details for each study phase are described in the following sections.

**Table 1 table1:** Construct and data collection used for pre- and postassessment of the interventional study.

Outcome and participants		Construct	Data collection instrument

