**Primary outcomes**			
	Patients and staff	Digital health literacy	DHLI^a^ (online self-assessment survey) GR-eHEALS^b^ (online self-assessment survey)
	Patients and staff	Digital and technical literacy	ICT^c^ Self-Concept Scale (online self-assessment survey) Brief Scale of Technological Readiness (online self-assessment survey) Digital Use survey (online self-assessment)
	Patients and staff	Readiness and ability to change	Readiness for Change survey (online self-assessment)
	Patients	Engagement	Duration and frequency of DiGA use (observer rating)

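### Engagement with the apps is a primary outcome hypothesised to improve, but with no usable pre-value, comparator or benchmark the stated pre-post analysis cannot test that hypothesis

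*Protocol article*

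**What the plan says.** Primary Outcome Measures names among the primary outcomes "their readiness and ability to change, as well as patients’ engagement with DiGAs". Table 1 lists it under primary outcomes, for patients only, as "Duration and frequency of DiGA use (observer rating", and its title reads "Construct and data collection used for pre- and postassessment of the interventional study". Abstract, Results, gives the directional hypothesis: support by digital navigators (DNs) is expected to enhance "digital and technical literacy, patient engagement with DiGAs, and readiness and ability to change".

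The article gives two accounts of when engagement is measured.

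- Data Collection and Analysis: "All primary and secondary outcomes will be assessed before and after the 12-week intervention (pre- and postassessment".
- Abstract, Methods: the constructs measured at both time points are listed without engagement, which has its own sentence: "Patient engagement with the DiGAs (usage duration and intensity) was measured after the intervention".

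The data source is stated in Primary Outcome Measures: "Engagement with DiGAs was assessed via structured interviews conducted by the study team". Phase III describes the quantitative analysis as a pre-post comparison by paired t-test or Wilcoxon signed-rank test at α = .05, with effect sizes and with regression to control for confounders. The same section counts the three months of DN support from the day the app is activated. Limitations states that there is no comparison group. No reference value for engagement is given anywhere in the article.

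**The concern.** A claim that something is enhanced needs a reference: the same patients earlier, a concurrent group, or a value fixed beforehand. The other primary outcomes at least have a baseline, because literacy and readiness for change can be scored before the app is prescribed. Use of the prescribed app cannot be scored in that way before it has been activated.

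Two outcomes are possible. The hypothesis may receive no test at all, or a comparison with zero may be reported as a significant increase. The second result would show only that some patients opened the app. Engagement is in the article's title, and Phase III asks how DNs affect use of the apps. An uninformative positive result could therefore be read as support for the roll-out described in the Discussion.

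**Working it through.** **Inputs.** 48 patients (Abstract, Methods; Phase III), which reproduces as 6 sites × 8 = 48. This is a feasibility number: Sampling says it was not derived statistically, so there is no power figure to reproduce. α = .05, with sidedness not stated; two-sided is assumed here. There is one group, and the start of use is app activation.

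**Step 1: engagement measured only afterwards.** Each patient has one value. A paired t-test or signed-rank test works on (post − pre), and there is no pre-value, so no test statistic exists. Regression for confounders does not supply the missing reference. What remains is one-sample estimation. For a mean, the 95% half-width is t(0.975; 47)/√48 ≈ 0.29 SD.

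**Step 2: engagement measured before and after, with zero entered as the pre-value.** Every difference is then ≥ 0. Patients with no use are ties and drop out. If k patients use the app at all, all k differences are positive, and the exact two-sided p-value is 2 × 0.5^k (the same for the sign test and the signed-rank test).

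| k users | p |
|---|---|
| 4 | 0.125 |
| 5 | 0.0625 |
| 6 | 0.031 |
| 7 | 0.016 |

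The test rejects at .05 once 6 of 48 patients (6/48 = 12.5%) have any use.

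**Step 3: how often that happens.** The article gives no expected uptake, so the true any-use rate q is an assumption. Patients are treated as independent, ignoring clustering by site. The rejection probability is P(X ≥ 6) with X ~ Binomial(48, q).

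| assumed q | P(reject) |
|---|---|
| 10% | 0.35 |
| 20% | 0.94 |
| 30% | 0.999 |
| 50% | ≈ 1.00 |

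These probabilities depend on uptake alone. No term represents what the DNs add to the use that would have occurred without them.

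**Step 4: what 48 patients can give.** For illustration only, suppose 36 of 48 (75%) were still using the app at the end. The Wilson 95% interval is centred at (0.75 + 3.84/96)/(1 + 3.84/48) ≈ 0.731, with half-width 1.96 × √(0.75 × 0.25/48 + 3.84/(4 × 48²))/(1 + 3.84/48) ≈ 0.119. The interval is 61.2% to 85.1%, which is a useful feasibility estimate.

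**The case against.** The strongest reply is that nobody intended a paired test of engagement. The abstract takes engagement out of its pre-post list, and the examples beside the paired tests in Phase III are digital health literacy and disease severity. The specific sentence should then outrank the blanket one. This is a fair reading. A reader might infer that the plan commits itself to testing engagement against zero, and the article does not say so. But the abstract follows its post-only sentence with a general statement that quantitative data were analysed pre-post, and two other places put all primary outcomes there. On the generous reading, moreover, the hypothesis has no test at all.

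Second, the limitations are disclosed: no comparison group, no power, and an aim of feasibility rather than effectiveness. That answers any suggestion that the missing comparator is hidden. The caveat, however, concerns attributing observed changes. For engagement with the study app no meaningful change can be observed, and the directional hypothesis still stands.

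Third, eligibility does not exclude earlier app use, and the assessment schedule (Multimedia Appendix 3) is not shown, so some question about earlier use may have been asked at baseline. Such use would concern another app or another episode and would not be a baseline for the study app.

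Two further inferences should be resisted. A reader might see a conflict between the structured interview and the observer-rating label in Table 1. There is none: the table uses that label to separate interviewer-collected data from online self-assessment, and Phase III says patients were interviewed about app engagement. A reader might also assume that app usage logs are available, because DNs process data from the apps. The sections on the DN role and training do not say that such logs were kept for research.

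**Conclusion.** The concern holds for the design as stated. The article contradicts itself on when engagement was measured, and on either account the pre-post paired analysis cannot test whether DN support enhances it. There is no paired difference on one reading. On the other, significance follows from any use by 6 of 48 patients.

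This rests on two premises: use of the study app before activation is zero or undefined, and no external benchmark exists outside the article. The rejection probabilities rest on assumed uptake. A reader might conclude that a significant result is practically certain. That is so from about 30% any-use upwards, but at 10% the probability is only about 0.35. The defect concerns one primary outcome and its hypothesis; the other primary outcomes do not share it. It leaves the value of engagement as a feasibility measure intact.

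**What to change.** - Reconcile Abstract (Methods), Data Collection and Analysis, and the Table 1 title by stating that engagement is measured after the intervention only and is exempt from the pre-post assessment and the paired tests.
- State openly that the hypothesis of enhanced engagement cannot be tested in this design, and treat engagement as a descriptive feasibility outcome. According to the Results section the intervention ended in June 2025. The published hypothesis should therefore not be silently removed, and a benchmark can no longer be set in advance.
- Report one-sample estimates with 95% confidence intervals from the post-intervention interview, for example the proportion who activated the app, the proportion still using it at week 12, and frequency of use. Keep all 48 enrolled patients in the denominator, with those who never activated or who stopped counted as non-use.
- Use one label for the components: the abstract has duration and intensity, Table 1 has duration and frequency.
- Use app-recorded usage as a supporting source only if it was retained and is available for research.

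The cost is revised text and no p-value for engagement. No new data are needed.

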**Results:**

The study received funding in July 2024. The prestudy including 35 participants was conducted from August to October 2024. HDNT adaptation and DN training were conducted from October to December 2024. Recruitment and quantitative baseline data collection started in December 2024, and 48 participants were enrolled by the end of March 2025. The intervention study ended in June 2025. Result dissemination and the development of strategies for the long-term implementation of DNs into the German health care system are planned until September 2025. We hypothesize that the provision of support by DNs will enhance patients’ and HCP’ digital and technical literacy, patient engagement with DiGAs, and readiness and ability to change. In addition, patients’ mental health is expected to improve after the end of the intervention.

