**Conclusions:**

This is the first study to examine the feasibility and effects of DNs in German health care. The study will provide significant insights into the acceptability and feasibility of human-facilitated competency development for mental health apps in multiprofessional health care teams and their patients. The successful implementation of DNs can promote the use of DTx in Germany and thus enhance access to and the provision of health care for individuals affected by a mental disorder.

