In Germany, DTx are called *Digitale Gesundheitsanwendungen* (“digital health apps” [DiGAs]) and have been available since the implementation of the Digital Health Care Act (*Digitale-Versorgung-Gesetz*) in December 2019 [36]. This legislation established the framework for the approval and reimbursement of digital mental health apps. These apps must meet specific standards set by the German Federal Institute for Drugs and Medical Devices (BfArM) to ensure safety, quality, functionality, privacy, data security, and effectiveness [37]. Once approved, DiGAs can be prescribed by physicians and psychotherapists and are reimbursed by statutory health insurances. Currently, there are 72 DiGAs available, of whom 29 (40.28%) focus on mental health conditions (eg, n=7, 24.14% on depression; n=7, 24,14% on anxiety). All approved DiGAs can be found in the publicly available German DiGA directory of the BfArM [38].

Although DNs have been successfully implemented in several countries [11,32], no such role or training program currently exists in Germany. In addition, evidence from abroad cannot be easily transferred to Germany since the introduction of new roles, such as DNs, must align with existing structures, including statutory health insurance and professional licensing laws. As a result, the best practices from other countries must first be adapted to the German legal, financial, and organizational framework [39].

An exploratory pilot trial is therefore needed to gather preliminary information about the implementation of DNs in the German health care system and the feasibility of conducting a full-scale trial. The aim of this study is to (1) explore the acceptance and expectations of HCPs and patients in Germany toward DNs (2); adapt the Harvard Digital Navigator Training (HDNT) for the German health care system; (3) evaluate the trial implementation of DNs, including their impact on patients and other HCPs; and (4) investigate options for perpetuating DNs in the German health care system.

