### Study Design

The DigiNavi study is designed as a multicenter, single-group, observational, mixed methods interventional study, incorporating elements of participatory design. This study consists of four research phases (see Figure 2): a prestudy (phase I), training of DNs (phase II), a 12-week intervention where DNs support the use of DiGAs (phase III), and steps toward integrating the DN role into the German health care system (phase IV). The following research questions will be addressed in the four phases:

Phase I: What are the levels of acceptance and expectations of HCPs and patients toward DNs?Phase II: What responsibilities and specific skills should DNs have in the German health care system? How can these findings contribute to the need-based introduction of this new role?Phase III: What impact does the advice and support provided by DNs have on the digital health literacy of patients and HCPs? What impact does the increased integration of DiGAs into treatment have on their use and the therapeutic relationship between patients and HCPs? What are the challenges and barriers that arise when piloting DNs?Phase IV: What measures are necessary to ensure the long-term implementation of DNs in the German health care system?

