#### Phase III: Pilot and Evaluate (Interventional Study)

In the intervention phase, the trained DNs trained the multiprofessional teams at the six study sites to select and integrate DiGAs for mental health into the treatment of 48 patients (n=8, 16.7%, per site). The DNs provided at least one training session for their teams. A guideline for this training was provided by the study team. Based on the findings from phases I and II, the content and structure of the intervention were finalized. It was established that selected patients would use a DiGA for 12 weeks and receive guidance and support from trained DNs during these 12 weeks, encouraging regular use of a DiGA tailored to their individual needs. To enhance adherence, participants were regularly asked about any challenges they encountered during check-up appointments with their DNs. To promote engagement, DNs suggested practical strategies, such as integrating DiGA use into daily routines or identifying suitable time frames for engagement. The study team supported the DNs through monthly web-based meetings. In these meetings, DNs received up-to-date information about the study progress, got an opportunity to ask questions, and exchanged experiences. During the intervention phase, DNs contacted the study team at any time if they had questions or encountered any issues. In addition, process data, such as the number and duration of contacts between patients and DNs, were collected during the intervention to enable the identification and validation of any qualitative differences in implementation at the different study sites.

The trained raters (n=6) conducted data collection with patients (N=48) and HCPs (N=18; n=3, 16.7%, per site) at each study site at two timepoints: before the 12-week intervention (preassessment), and directly after completing the intervention (postassessment). The end of the intervention phase was defined as the date of DiGA activation plus a 3-month DN support period. The study team also met with the raters once a month in a web-based meeting to discuss the progress of the preassessments and later postassessments. During these meetings, raters got an opportunity to ask questions and receive assistance with any issues or challenges they may have encountered.

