In addition, the study is being conducted without a comparison group (ie, with only one condition). This makes it difficult to identify and control for confounding factors and to attribute observed changes, such as in digital literacy or psychological health, clearly to the intervention. However, the primary goal of the DigiNavi study is to investigate the feasibility of the innovation, not to provide evidence of its effectiveness. The sample size and composition chosen are therefore justified by the exploratory nature of the planned study and are appropriate for a pilot project. The implementation of a larger randomized controlled trial may be a future goal for research efforts to assess effectiveness and causal relationships.

Furthermore, the limited funding period of only 14 months has resulted in the intervention phase being constrained to a duration of 3 months per patient. As a result, the study design does not include a follow-up component, precluding any assertions regarding the evolution of the outcomes of interest over a 6- or 12-month period.

Further studies are needed to test DNs in inpatient and outpatient settings, or in the somatic field, to determine whether the hypothesized effects of DNs can be confirmed in other settings and patient groups and whether DNs can be established as a sustainable tool for improving the care of patients with mental health conditions. In addition, further international studies involving different health care systems would be of great value. The findings of this study, together with the easily accessible training materials on the project website [71], should encourage and facilitate further research.

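### Every patient gets a DiGA and navigator support together, so patient literacy, readiness and engagement results cannot be credited to the navigators, yet the plan words them that way

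*Protocol article*

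**What the plan says.** The design is stated plainly under Study Design: "The DigiNavi study is designed as a multicenter, single-group, observational, mixed methods interventional study". The section on Phase III (Pilot and Evaluate) says that each patient uses a DiGA for 12 weeks with DN guidance throughout, and counts the end of the intervention from DiGA activation plus three months of DN support. The Abstract (Methods) confirms that the assessment window spans both components: outcomes were "assessed before and after 12 weeks of DTx prescription and support by DNs".

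Four places name the navigator as the cause of what is observed:

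- Abstract, Results: "We hypothesize that the provision of support by DNs will enhance patients’ and HCP’ digital and technical literacy". The same sentence adds patients' engagement with DiGAs and readiness and ability to change.
- Study Design, first Phase III question: "What impact does the advice and support provided by DNs have on the digital health literacy of patients and HCPs".
- Primary Outcome Measures: the first primary outcome is defined as the impact of DNs on the digital health literacy of patients and health care professionals (HCPs).
- Abstract, Conclusions: "This is the first study to examine the feasibility and effects of DNs in German health care".

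The document treats the app as active in its own right. The Introduction calls digital therapeutics evidence-based and says approved DiGAs must meet standards "to ensure safety, quality, functionality, privacy, data security, and effectiveness".

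The Limitations acknowledge that "the study is being conducted without a comparison group (ie, with only one condition", that attributing change to the intervention is therefore difficult, and that the goal is feasibility rather than effectiveness.

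**The concern.** For a patient, the pre-post contrast compares the state before the study with the state after 12 weeks of app and navigator combined. The hypothesis, question and primary outcome are about one of those two components. Twelve weeks of using a health app could plausibly change how someone rates their own digital skills or readiness for technology, with or without a navigator. The document neither supports nor excludes this.

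What is at stake is how the result is read. A positive change in a primary outcome defined as the impact of DNs, tested at α=.05, would naturally be reported as a navigator effect. The data would be equally compatible with an effect of the app, of the two together, or of time.

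**Working it through.** **Stated sample.** Six sites × 8 patients = 48 patients; six sites × 3 HCPs = 18 HCPs. Both agree with the document. It gives no power, effect size or SD to reproduce.

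**Patients: what the pre-post change estimates.** Write the mean change as

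Δ = A + N + AN + T,

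where A is the effect of DiGA use, N that of DN support, AN their interaction, and T everything that changes without either (time, regression to the mean, retesting). The study observes a single Δ per outcome. N could be isolated only if some patients had A without N, and none do.

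**Can the planned regression separate them?** The Phase III section plans multiple linear regression to control for confounders. Indicators for DiGA use and for DN support would both equal 1 for all 48 patients. Each is identical to the intercept column, so neither coefficient is estimable. Covariate adjustment does not change this.

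**Engagement.** The Abstract (Methods) says it was measured after the intervention. The study therefore observes one level, under DiGA plus DN. To say that DNs enhanced it requires the level under DiGA without DN, which is not observed.

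**HCPs.** They are not prescribed a DiGA, so the patient bundling does not apply. Their change is still N + T with no control group, so N is not identified there either.

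**DN contacts.** The Phase III section says "process data, such as the number and duration of contacts between patients and DNs, were collected during the intervention". This is the only variation in DN exposure among patients. It is not assigned by design, and patients in more difficulty are likely to have more contacts, so a gradient would be confounded by need.

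**Illustration.** Set N = 0 and AN = 0. Let d be the mean of A + T divided by the SD of the individual changes. The assumptions are a two-sided paired t-test at α=.05 (the document does not state sidedness), all 48 patients assessed twice, and d from 0.2 to 0.5 (the document gives none). The noncentrality is d√48 = 6.93d with 47 degrees of freedom.

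| Assumed d | Noncentrality | Probability of p<.05 with no DN effect |
|---|---|---|
| 0.2 | 1.39 | 0.27 |
| 0.3 | 2.08 | 0.53 |
| 0.4 | 2.77 | 0.78 |
| 0.5 | 3.46 | 0.92 |

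This shows that significance would not be evidence for N. It does not estimate the size of any misattribution. Because d includes time effects, part of it reflects the missing control group, which the document already discloses.

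**The case against.** The strongest defence is that the limitation is largely disclosed. The Limitations section says that with one condition, changes in digital literacy or psychological health are hard to attribute to the intervention. It adds that causal inference is constrained, recommends a randomized trial, and gives feasibility as the goal. The package is also described openly: the section on the complex intervention presents DN work as interacting components, and helping to select and use apps is part of the DN role. Evaluating such a package as a whole in a pilot is legitimate. All of this stands. It does not cover the remaining gap, because the concession concerns the intervention as one unit. A later trial of DN-supported DiGA use against usual care would meet the stated limitation and still not isolate the navigator. The DN-effect wording of a tested primary outcome also remains.

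Four stronger readings might be inferred, and the document does not support them:

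- *Symptom improvement is claimed as a DN effect.* It is not. The Abstract says separately that mental health is expected to improve after the intervention, and severity is a secondary pre-post outcome without DN attribution. The effectiveness standard for DiGAs says nothing about digital literacy.
- *The navigator's marginal effect is the study's one question.* The stated aims also cover acceptance, training adaptation, implementation and continuation, and the second Phase III question concerns DiGA integration.
- *Accreditation or remuneration depends on the pre-post result.* The Phase IV section describes both as under preparation and sets no such condition.
- *DN-impact wording is safe for HCP and engagement outcomes.* HCP change is uncontrolled, and engagement has no DiGA-only reference level.

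**Conclusion.** The point holds for patients' digital health literacy, digital and technical literacy, readiness to change, and engagement. The design cannot credit results on these outcomes to DNs, and the Abstract, the first Phase III question and the first primary outcome are worded as if it could; the Abstract's conclusion adds to this by referring to effects of DNs. This follows from the design alone and rests on no numerical assumption.

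The size of any misattribution is unknown. The probabilities of 0.27 to 0.92 depend entirely on assumed changes of 0.2 to 0.5, and that app use alone raises self-rated literacy is plausible but undocumented. The mental-health hypothesis is outside the point. The single-group design is acceptable for a feasibility pilot; the fault lies in the claims attached to it and in a limitation that stops one step short. The change is worth making because it alters what the study may conclude and costs almost nothing.

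**What to change.** Leave the outcomes, instruments and tests as they are and change what is claimed, including in the results report:

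1. Restate the patient hypotheses, the first Phase III question, the first primary outcome and the conclusion as change under DN-supported DiGA use.
2. Describe engagement as the level observed under DN support, not as enhanced by it.
3. Describe HCP results as uncontrolled pre-post change, also without causal DN wording.
4. Add to the Limitations that the intervention combines a separately active app with the navigator, so even a change attributable to the intervention could not be assigned to the DN. Note that a future trial needs a DiGA-without-DN arm if the navigator's contribution is the question.
5. Optionally, tabulate patient change by DN contacts, using the process data already collected. State that the pattern is confounded by need and does not isolate the DN contribution.

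The cost is a few sentences and, for item 5, one descriptive table. The downside is a more modest claim about navigators.
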